### Characteristics of participants

Baseline characteristics will include sociodemographic information, symptoms duration, number of pain areas, family history of low back pain, magnetic resonance imaging (MRI) performed, chronicity risk (Örebro Musculoskeletal Pain Questionnaire [OMPQ]), history of Pilates method practice, and life stress events (Table 3). Baseline characteristics (e.g. history of Pilates method practice) may be analyzed as potential predictors or moderators of outcomes.

**Table 3 Tab3:** Characteristics of participants

1) Sociodemographic data, including age and sex, will be obtained; 2) Duration of low back pain (in months) will be obtained through the question: “How long have you had low back pain?”; 3) Risk of chronicity, obtained through the 10 items of the short version of the Örebro Musculoskeletal Pain Questionnaire (OMPQ)[30]; 4) Map of pain regions, where the participant will mark the numbers that correspond to the pain site; 5) Life stress events assessed through closed questions, with dichotomous answers (yes and no), covering the following aspects: serious illness that resulted in withdrawal from usual activities; hospital admission due to illness or accident; death of a close relative; severe financial problems; forced change of housing; separation/divorce; Physical aggression; and assault/robbery; 6) MRI performed, where the following question will be asked: “Have you ever performed a magnetic resonance imaging (MRI) for the lumbar spine?” Answer options: yes or no; 7) Family history of low back pain, where the following question will be asked: “Do you have anyone in the family who suffers from low back pain?” Answer options: yes or no; 8) History of Pilates method practice, where the following question will be asked: “Have you ever practiced Pilates?” Answer options: yes or no.	

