### Statistical analysis

The analysis of the data obtained during the research will be carried out by a statistical professional who will have access to the coded data and were based on intention-to-treat principles. Missing data will be assumed to be missing completely at random. Multiple imputation will be used to account for these missing data [33]. Missing values in outcome variables will be estimated using multiple imputation by chained equations after 50 replicated imputed data sets. Variables included in the multiple imputation process will include (1) group factor, (2) time factor, and (3) the respective outcome variable. Descriptive statistics will be used to present the characteristics of participants in the two treatment groups. Two-sided *P* values of less than 0.05 will be considered to indicate statistical evidence of significance. The outcomes pain intensity and disability will be analyzed using repeated-measure linear mixed models (participants and time as random factors) that included all the scores that will be reported after randomisation with the baseline scores and treatment clusters as covariates. Adjusted mean differences will be tested at 12 weeks after randomisation. Multiple comparisons will be performed using the Tukey test with *P* values adjusted using the Holm procedure. The baseline variables will be evaluated as predictors and moderators of treatment effects including terms and interaction models. Effect sizes for primary and secondary outcomes will be calculated as Cohen’s d from estimated marginal means and standard error estimates from the primary adjusted analysis. Effect sizes will be interpreted according to Cohen’s criteria (small ≤0.2; moderate = 0.5; large ≥0.8) [34]. All analyses will be performed using the RStudio version 0.99.486.

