### Sample size estimation

The sample size required for this study will be 152 (76 per group) to detect a mean difference of 4.0 points for disability measured by RMDQ and 1.0 for pain intensity measured by NPRS between the two intervention arms, assuming a standard deviation of 4.9 for disability and 2.0 for pain, with an alpha of 5%, power of 80% and a possible loss to follow-up of 15 % [35–37].

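### Chronicity risk and pain duration are recorded before randomisation but left out of the primary models; prespecifying them as covariates could modestly sharpen the pain estimate at almost no cost

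*Protocol article*

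**What the plan says.** The Statistical analysis section of the protocol article analyses both co-primary outcomes with repeated-measures linear mixed models, "with the baseline scores and treatment clusters as covariates". It names no other covariate.

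Two further variables with an obvious claim to be prognostic are collected at baseline. Table 3 lists "Risk of chronicity, obtained through the 10 items of the short version of the Örebro Musculoskeletal Pain Questionnaire (OMPQ"), and the duration of low back pain in months. Table 1 places both at the baseline visit. Treatment allocation and randomisation has the envelope opened only after baseline data are collected, so both are valid pre-randomisation covariates. That section describes blocks and mentions no stratification.

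Their stated use is different: "Baseline characteristics (e.g. history of Pilates method practice) may be analyzed as potential predictors or moderators of outcomes". The Statistical analysis section repeats this role. The imputation model there contains only arm, time and the outcome being imputed.

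The Sample size estimation section asks for 76 per group. The difference to be detected is 4.0 RMDQ points in disability and 1.0 point in pain; the assumed SDs are 4.9 and 2.0 respectively. The remaining inputs are given as "with an alpha of 5%, power of 80% and a possible loss to follow-up of 15" per cent.

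**The concern.** A covariate measured before randomisation that predicts the outcome reduces the residual variance of the treatment comparison and corrects for chance imbalance in that variable. Here the data will already be in hand, and the article itself labels one of the variables as a measure of risk. Leaving both out of the primary models may cost precision on pain, where the unadjusted sample size calculation lands almost exactly on its 80% target. Disability has ample power, so little is at stake there.

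There is a second, smaller issue. About 15% of participants may be lost. If loss is related to prognosis, the planned imputation and analysis models can draw on the baseline outcome score but not on chronicity risk or duration.

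**Working it through.** **Inputs from the Sample size estimation and Statistical analysis sections.** Two-sided alpha 0.05; power 80%; pain difference 1.0, SD 2.0; disability difference 4.0, SD 4.9; 15% loss; 76 per group.

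**Inputs the article does not give, so assumed.** r, the correlation of baseline with 12-week pain: 0.3 or 0.5. R², the share of residual variance explained by the added covariates once baseline pain is in the model: 0 to 0.15.

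**Step 1: reproduce the plan's figure.** For pain, a two-sample t-test with standardised difference 1.0/2.0 = 0.5 needs 64 per arm (power 80.1%). Allowing for loss, 64/0.85 = 75.3, rounded up to 76 per arm and 152 in total, as stated. For disability, 24 to 25 per arm are enough, or 58 to 60 in total after the allowance for loss; power at 64 per arm is about 99.6%. So pain sets the sample size, and the calculation uses the raw SD without any covariate adjustment.

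**Step 2: effect of the added covariates.** Residual SD = 2.0 × √[(1 − r²)(1 − R²)]. The further reduction in SE is 1 − √(1 − R²), whatever r is. The equivalent gain in participants is 1/(1 − R²) − 1. Power for a 1.0-point difference with 64 completers per arm (normal approximation) is Φ(1.0/[residual SD × √(2/64)] − 1.96). Clustering is ignored in this table.

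| R² of added covariates | SE reduction | Equivalent extra participants | Power, r = 0.3 | Power, r = 0.5 |
|---|---|---|---|---|
| 0 (planned model) | 0% | 0% | 84.3% | 90.4% |
| 0.02 | 1.0% | 2.0% | 85.0% | 91.0% |
| 0.05 | 2.5% | 5.3% | 86.0% | 91.8% |
| 0.10 | 5.1% | 11.1% | 87.8% | 93.1% |
| 0.15 | 7.8% | 17.6% | 89.5% | 94.3% |

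Worked example for r = 0.3, R² = 0.10: residual SD = 2.0 × √(0.91 × 0.90) = 1.810; SE = 1.810 × 0.1768 = 0.320; 1.0/0.320 − 1.96 = 1.165, and Φ gives 87.8%. The half-width of the 95% interval falls from 0.661 to 0.627 points.

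**Step 3: degrees of freedom.** With the SD unchanged, spending two degrees of freedom moves t-test power at 64 per arm from 80.15% to 80.14%. The cost is negligible even if the covariates turn out to be useless.

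**Step 4: chance imbalance.** With 76 per arm, the probability that the arms differ by more than 0.3 SD in OMPQ score is 2 × [1 − Φ(0.3/√(2/76))] = 2 × [1 − Φ(1.85)] = 6.4%.

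**The case against.** The strongest reply is that nothing is wrong. The plan prespecifies a short covariate set that includes the baseline score of the outcome, usually the natural first choice. Leaving out further covariates does not bias a randomised comparison and contradicts nothing in the article. The benefit rests wholly on an assumed R². A risk-of-chronicity label does not show that the score predicts 12-week pain beyond baseline pain, particularly as everyone enrolled already has pain of more than three months. All of this stands, and it is why the point is an improvement and not an error.

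The reply does not remove the point. The article fixes the covariate list itself and does not defer it to another document. The two variables cost nothing to collect, and Step 3 shows that including them costs next to nothing.

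A second reply is that baseline adjustment already lifts power for pain to about 84% to 90%. That is right as far as it goes, but the figure ignores treatment in groups of up to six. As an illustration, assume clusters of 6 and an intraclass correlation of 0.02 to 0.05. The design effect is 1 + 5 × ICC = 1.10 to 1.25, so 64 per arm count as 58.2 to 51.2. At r = 0.3 power is then 81% to 76%, and covariates with R² = 0.10 bring it to 85% to 80%. At r = 0.5 the figures are 88% to 83%, and 91% to 87%. The margin may therefore be thinner than it looks, but the article gives no intraclass correlation.

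**Conclusion.** The primary models leave out two baseline variables that could improve precision, and adding them is worthwhile because it is nearly free. The likely size is modest: a fall in SE of about 1% to 8% for an assumed R² of 0.02 to 0.15. Before clustering, that is about 0.7 to 5.2 points of power at r = 0.3 and 0.6 to 3.9 points at r = 0.5. If R² is zero there is no gain.

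A reader might infer more, and the article does not support it:

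- *Precision is certainly being lost.* No figure is given for the prognostic strength of either variable.
- *Pain has no reserve of power.* That describes the unadjusted calculation, not the planned model, which already adjusts for baseline.
- *Chance imbalance is unprotected.* Baseline-score adjustment covers that variable, and a 6.4% chance of a 0.3 SD difference is ordinary randomisation variation already reflected in the SE.
- *A complete-case estimate is at risk.* Multiple imputation is planned. The relevant point is narrower: the imputation model lacks these variables.
- *Covariates will be picked from the predictor analysis.* The article does not say that selected predictors will enter the primary result.
- *The other co-primary's baseline score is excluded.* The plural in the covariate statement leaves open whether each model uses one baseline score or both.

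**What to change.** In the Statistical analysis section, before outcome data are analysed by group:

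- Keep the baseline outcome score and treatment clusters in both primary models. The clusters must not be dropped when the list is extended: with group sessions, omitting them could make the SE too small and outweigh any gain.
- Add the short OMPQ score and the logarithm of pain duration in months as main effects. Add the other co-primary outcome's baseline score if it is not already included, and say which baseline scores enter each model.
- State that these terms stay in whatever their P values and are not chosen from the predictor or moderator analyses.
- Put the same variables in the imputation model.
- Report the currently planned model, with baseline scores and treatment clusters, as a sensitivity analysis.

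The cost is two or three model degrees of freedom and a little analysis work. No new data are needed and the sample size does not change.

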### Sample size estimation

The sample size required for this study will be 152 (76 per group) to detect a mean difference of 4.0 points for disability measured by RMDQ and 1.0 for pain intensity measured by NPRS between the two intervention arms, assuming a standard deviation of 4.9 for disability and 2.0 for pain, with an alpha of 5%, power of 80% and a possible loss to follow-up of 15 % [35–37].

## Discussion

The results of this study will contribute to the understanding of the effectiveness of education to keep the abdomen relaxed versus contracted during Pilates method exercises in the treatment of primary chronic low back pain. Pilates is commonly used as an effective treatment for low back pain [38]. In Brazil, the Pilates method is widely disseminated, including practitioners of different profiles and age groups. It is used by physiotherapists for the prevention, recovery, and maintaining the overall functioning of the body.

There are no comparisons between these different strategies during the practice of Pilates method exercises – education based on a contraction versus relaxation of the abdomen. In this sense, aiming to understand the value of each component and increase the effect size of Pilates treatment, the result of a randomised controlled clinical trial of high methodological quality will help physical therapists in the clinical decision-making process.

There will be no objective measure of abdominal muscles activation in our study. However, regardless of whether the participant is able to activate the muscles as requested by the physiotherapist, the instruction for contracting the abdominal itself is an instruction for protecting the lower back during the exercises as opposed to the experimental group.

The sample size of this study will be sufficient to detect the relevant effects of different protocols conducted with a low risk of bias. Increasing the relevance of the study, the exercise protocol will be designed to reproduce the same format in which they would be conducted in the clinical practice by a certified physical therapist. The conclusions of this study may contribute to the existing literature for the treatment of patients with primary chronic low back pain with Pilates.

## Trial registration in a clinical trials database

This study was prospectively registered in the Clinical Trials (Registration number: NCT05336500) and approved by the Human Research Ethics Committee (Plataforma Brasil CAAE 25669519.4.0000.5116). Recruitment begins in May 2022 and is expected to continue until March 2023.

## Data Availability

All data measured and/or manipulated during the study will be available by the corresponding author on reasonable request. Patients will be accompanied by the physiotherapist responsible for their treatment. All possible adverse effects or events during the intervention will be recorded daily. An auxiliary researcher will act as data coordinator at baseline and during reassessments, being responsible for all the processes involved until the end of the research (completion of tables and data processing). All documents will be stored in a safe place, being accessible only to the researchers involved. Electronic data will be protected on a computer with a restricted password and access, and only authorized researchers will be able to handle them. All names or personally identifiable information will be encoded. The statistician who will do the final analysis will receive the coded data.

## Abbreviations

CAPES: Coordenação de Aperfeiçoamento de Pessoal de Nível Superior
FAPERJ: Fundação Carlos Chagas Filho de Amparo à Pesquisa do Estado do Rio de Janeiro
KAC: Education to keep the abdomen contracted
KAR: Education to keep the abdomen relaxed
NPS: Numerical Pain Scale
OMPQ: Örebro Musculoskeletal Pain Questionnaire
PGES: Perception of Global Effect Scale
PSFS: Patient-specific functional scale
RMDQ: Roland-Morris Disability Questionnaire
